Appendix S2 – ONCODAGE study protocol (abridged translation from French)

| **Study title** | Validation of a geriatric screening tool in oncology |
| --- | --- |
| **Acronym** | **ONCODAGE** |
| **Coordinating centre** | Institut Bergonié, Centre de Lutte Contre le Cancer, Bordeaux. |
| **Coordinator** | Pr. [name] |
| **Number of centres** | At least 15: the 15 Pilot Units of Coordination in Geriatric Oncology (*UPCOG*) along with health institutions members of the oncology network. |
| **Indication** | Patients over 70 years old with a cancer (colon, lung, ENT, breast, prostate, lymphoma), as part of the initial management. |
| **Trial rationale** | As patients age, risks for serious toxicity, or even lethality, during cancer treatment increase. A detailed assessment of the patient’s status is required.  Comprehensive geriatric assessment (CGA) is a method which has proved its usefulness but which is time-consuming and expensive to administer. A screening tool allowing the individualisation of patients who would benefit from a CGA is necessary.  In a previous regional prospective multicentre cohort (regional Ministry of Health-financed project, PHRC 2003), we studied patients over 70 years with cancers who were receiving first-line chemotherapy. This study enabled us to perform an exploratory study in order to develop a screening tool, the G8, which consists of a 7-item questionnaire from the Mini Nutritional Assessment (MNA) and an age indication. We applied the suggested screening tool to our population of 364 patients and this analysis provided encouraging results to be studied on a wider scale (Bellera et al., Ann Oncol, 2012). |
| **Expected effects** | With the use of this simple tool for screening, to be administered by nurses or oncologists, we consider that more elderly patients with cancer will be able to benefit from a CGA.  This tool will also enable us to rationalise the use of our geriatric assessment means and thus to focus their use on those who need it more, for more efficacy. |
| **Main objective** | Validate a new screening tool, the G8, to identify within a population of over 70-year-old patients with cancer those who need further geriatric assessment. |
| **Secondary objectives** | - **Validate the French version of the Vulnerable Elders Survey screening tool (VES-13).** - For each suggested screening tool, G8 and VES-13: - Assess the intrinsic qualities of the screening tool (internal consistency, reproducibility, and predictive value), - Assess the screening tool for specific populations (type of cancer, therapeutic strategy, stage of the disease). - Assess the number and type of suggested interventions according to the CGA - Compare both new suggested tools (VES 13 and G8). - Defining standards for tests and questionnaires used, for which no standards are available (G8, VES-13, MMSE, Timed up and Go, QLQ-C30) in a French population of elderly patients with cancer. |
| **Study design** | National multicentre prospective cohort study suggested to the 15 UPCOG and to health institutions members of oncology networks. |
| **Number of patients** | In order to ensure a minimum of 1500 assessable patients, we will recruit **1650 patients**. |
| **Inclusion criteria** | 1. 70-year-old patients or more,  2. Cancer proved histologically, irrespective of grade or stage,  3. The following tumour types: colon, lung, ENT, breast, and lymphoma,  4. As part of an initial therapeutic management, whether it is medical (chemotherapy, hormone therapy, targeted treatment), surgical, or radiotherapeutic,  5. Management by one of the 15 UPCOG or teams associated to the project,  6. Patients who received the information leaflet and signed the informed consent form,  7. Patients registered with a social security scheme. |
| **Non-inclusion criteria** | 1. Persons deprived of freedom or under tutelage,  2. Presence of a psychological, familial, social, or geographic condition which might disturb the right course of the study. |
| **Course of the study** | **Oncological assessment consultation** *(oncologist and nurse)*   - Information leaflet and informed consent, - Assessment of eligibility criteria, - Standard clinical examination (oncologist), - G8 questionnaire (oncologist), - VES-13 self-questionnaire (nurse), - Organisation of appointments for oncological assessment (pre-therapeutic evaluation, extended assessment), and geriatric oncologic assessment.   **Oncological assessment**  The oncological assessment is the extended and standard pre-therapeutic assessments usually performed for patients. Clinical and paraclinical data will be collected for the study.  **Geriatric oncologic assessment** *(geriatrician and geriatric assessment nurse for UPCOG)*  Before starting the oncological treatment and before setting up specific management, within two weeks at least after the oncological assessment consultation.  The nurse (IEG) will have to:   - Filling ADL, IADL, MNA questionnaires, along with the socio-cultural assessment score, - Performing the MMS and Timed Get up and Go tests, - Filling GDS-15 and QLQ- C30 self-questionnaires.   The geriatrician will then receive the patient for an oncological geriatrics consultation and will be in charge of the CIRS-G questionnaire, the synthesis of the self-questionnaires, the oncological geriatrics assessment, and of the clinical file. The doctor will try to recognise the patient for who the setting of a personalised programme of geriatric interventions is required.  **It is essential for the geriatrician not to have access to the G8 nor to the VES-13.**  **Follow-up**  Patients will be followed over 5 years. Data collection will be done at 1 and 5 years in order to collect data on vital status, disease progression, lifestyle (ambulatory, institutionalised). |
| **Summary of the study course** | **Step 1: Inclusion (J0)**  (Medical oncologists, surgeons, radiotherapists...)  _ Information leaflet  _ Informed consent  _ Inclusion and non-inclusion criteria  _ Inclusion form  **Step 1: Initial oncologic consultation (J0)**  (Medical oncologists, surgeons, radiotherapists...)  _ Booking an appointment for the geriatrics consultation  _ General information on the patient  _ Information on cancer  _ G8 questionnaire  _ VES-13 self-questionnaire  **Step 2: Oncological extended assessment (J0-J30)**  _ Biological data  **Step 3: Geriatrics consultation (J1-J30)**  (Geriatrician and nurse)  _ Geriatric assessment:  _ MMSE  _ ADL, IADL  _ GDS-15  _ QLQ-C30, sociocultural assessment  _ Timed Get up and Go  _ MNA  _ CIRS-G  _ Geriatrician’s recommendations  VES-13 again for 60 patients/centre in three centres:  Bordeaux, Lille and Lyons  **Step 4: Follow-up at 1 and 5 years**  Follow-up data collection (vital status and lifestyle) |
| **Assessment criteria** | **Principal assessment criteria**  G8 assessment will be performed using as a gold-standard tool the complete CGA based on the following tests, questionnaires, and scales: CIRS-G, ADL and IADL scales Timed Get up and Go test, MNA, MMS, and GDS-15.  Especially, we will consider a patient as being at risk or requiring a complete CGA if we observe at least one of the following conditions:   - CIRS-G: at least one grade ≥ 3 comorbidity (except treated cancer), - ADL scale: a score below or equal to 5, - IADL scale: a score below or equal to 7, - Timed Get up and Go test: time strictly over to 20 seconds, - MNA: a score below or equal to 23.5, - MMSE: a score below or equal to 23, - GDS-15: a score over or equal to 6.   We will assess, for various thresholds of the assessed tool, the performances of the new screening tool compared to the reference one, thanks to the following parameters:   - Sensitivity and specificity, - Youden’s index (J), - The predictive values (positive or negative), - The diagnostic likelihood ratios (positive or negative), - The area under the ROC curve.   **Secondary assessment criteria**   - The validation of the French version of the VES-13 screening tool will be based on the same validation criteria than for G8 tool. - The assessment of the intrinsic qualities of G8 and VES-13 tools will be based on the accuracy (internal consistency, reproducibility) and validation assessment. - The assessment of screening tools in various clinical situations will be based on the estimation of sensitivity, specificity, and of predictive values of each screening tool according to: - the type of cancer, - the therapeutic strategy (locoregional, and locoregional and adjuvant treatment), - the stage of the disease (local, metastasis). - We will evaluate the number of interventions according to the CGA (change of the initial treatment irrespective of its nature, interventions of other specialists in other fields). |
| **Hypotheses and statistical analyses** | **Hypotheses and required number of patients**  The objective is to maximise the sensitivity of the new screening tool and to obtain an estimation with a satisfying accuracy. Our exploratory study suggests (section 8) a sensitivity of about 90%, when we use as gold standard the presence of an abnormal score for at least one questionnaire, and a prevalence of 50% of patients with at least one abnormal questionnaire.  The inclusion of 1500 patients would help estimating the sensitivity on a 750-patient sample with abnormal CGA, with an accuracy of 2.4% for an expected sensitivity of 90% (*i.e.* 95% CI of 87.6% to 92.4%). In order to ensure a minimum of 1500 assessable patients, we will recruit **1650 patients**.  **Statistical analyses**  The population of the study will be described broadly according to its clinical and sociodemographic characteristics in terms of size and ratio for the qualitative variables and in terms of distribution for the quantitative ones.  The following parameters will be estimated:   - The sensitivity, the specificity, and the predictive values will be estimated. 95% CIs will be reported (binomial distribution). - The ROC curve representing graphically the sensitivity according to the (1 -specificity) for various thresholds of the assessed test will be represented graphically and help determine the area under the curve (AUC). - Internal consistency will be assessed according to Cronbach’s alpha coefficient. A 95% CI will be reported. - Reproducibility will be assessed by the intraclass correlation coefficient for quantitative variables. For qualitative variables, reproducibility will be assessed by Cohen’s kappa. - Scores between acknowledged subgroups will be compared thanks to a variance analysis. - Both G8 and VES-13 questionnaires will be compared thanks to their respective area under the curve. - We will assess whether using both screening tools together (G8 and VES-13) helps obtaining a more effective screening tool compared to the sole use of one questionnaire. |

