**3.4 STATISTICAL FACTORS**

**3.4.1 Hypotheses and required number of patients**

3.4.1.1 Main analysis

For a screening tool, sensitivity and specificity are assessed jointly, although we tend to favour sensitivity as it could be damageable not to detect patients requiring a CGA. The objective then is to maximise the sensitivity of the new screening tool.

Our exploratory study suggests (Chapter 9):

a sensitivity of about 90%, when we use as gold standard the presence of an abnormal score for at least one questionnaire,

a prevalence of 50% of patients with at least one abnormal questionnaire.

Supposing that the real sensitivity for our G8 screening tool is 90%, we estimate that the inclusion of 750 patients with at least one abnormal questionnaire would be enough to estimate the sensitivity with a sufficient accuracy (2.4%) and to obtain a 95% CI between 88% and 92%. Supposing that 50% of our population will have at least one abnormal questionnaire, **1500 assessable patients** will be needed.

A patient is said to be assessable if CGA and G8 data are complete. In our exploratory study, only 309 patients out of 364 had all the necessary questionnaires for CGA (85%). In order to ensure a minimum of 1500 assessable patients, we will recruit 1650 patients.

If we want to estimate sensitivity according to the type of cancer, we will obtain an accuracy of +/- 6% for a sample of 200 patients (95% CI: 84% to 96%), and of about 5% for a sample of 400 patients (95% CI: 86% to 94%).

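### The stated precision figures mix two interval methods: 87.6–92.4% matches neither, and about 5% for 400 patients contradicts its own 86–94% (minor)

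*Protocol*

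**What the plan says.** The main sample size is argued from the precision of the sensitivity estimate. The synopsis (Appendix S2, row on hypotheses and statistical analyses) bases it on "estimating the sensitivity on a 750-patient sample with abnormal CGA", "with an accuracy of 2.4% for an expected sensitivity of 90" per cent, and prints a "95% CI of 87.6% to 92.4" per cent. Section 3.4.1.1 states the same target with a rounded interval: "to estimate the sensitivity with a sufficient accuracy (2.4%) and to obtain a 95% CI between 88% and 92" per cent.

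The step from 750 to 1500 assessable patients uses a prevalence of one half: "Supposing that 50% of our population will have at least one abnormal questionnaire".

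Section 3.4.1.1 then gives two figures for estimates by type of cancer: "an accuracy of +/- 6% for a sample of 200 patients (95% CI: 84% to 96" per cent, and "of about 5% for a sample of 400 patients (95% CI: 86% to 94" per cent. It does not say whether these 200 and 400 are all patients or only those with an abnormal CGA.

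For the analysis, the synopsis says "95% CIs will be reported (binomial distribution", and section 3.4.3 repeats the binomial distribution for sensitivity and specificity. Neither place says whether the interval is exact or a normal approximation.

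**The concern.** A 95% interval for a proportion of 90% can be checked directly. A normal interval is symmetric about 90%. An exact binomial interval is not: its lower arm is longer than its upper arm. The synopsis prints a symmetric interval whose half-width does not match 750 patients. The 400-patient statement gives a half-width and an interval that disagree with each other.

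The main size rests on precision and not on a hypothesis test, so the headline figure should follow from its own inputs. The protocol also says that missed patients are the main worry, which makes the lower limit of sensitivity the one a reader will look at. If the printed figures come from different methods, the reader cannot tell which limit to expect from the analysis, least of all in the tumour-type subgroups, where the methods differ most.

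**Working it through.** **Inputs.** Expected sensitivity 0.90 and 750 abnormal patients (synopsis); prevalence 0.50 (synopsis and section 3.4.1.1); samples of 200 and 400 patients for tumour types (section 3.4.1.1); two-sided 95% level.

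**Formulas.** Normal: half-width = 1.96 × √(0.90 × 0.10 / n). Exact (Clopper-Pearson), for x positives out of n: lower limit = 2.5% quantile of Beta(x, n − x + 1); upper limit = 97.5% quantile of Beta(x + 1, n − x).

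**Step 1: the headline figure, n = 750.**
- Normal: 1.96 × √(0.09/750) = 2.15 points, so 87.85–92.15%.
- Exact, 675/750: 87.63–92.05%, with arms of 2.37 down and 2.05 up.
- Printed: 87.6–92.4%, ±2.4.

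The printed lower limit equals the exact one, and 2.4 equals the exact lower arm after rounding. The printed upper limit is not reached by either method. Wilson, Agresti-Coull, Jeffreys and the continuity-corrected normal interval were also tried; across all methods the upper limits run from 91.95% to 92.21%. A normal half-width of 2.4 points belongs to 1.96² × 0.09 / 0.024² ≈ 600 patients. The simplest explanation is that the exact lower arm was mirrored upwards.

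**Step 2: 400 patients, 200 of them abnormal.**
- Normal: 1.96 × √(0.09/200) = 4.16 points, so 85.8–94.2%. This is the printed 86–94%.
- Exact, 180/200: 84.98–93.78%, with arms of 5.02 down and 3.78 up. The lower arm is the printed value of about 5%.

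The accuracy thus appears to come from the exact method and the interval beside it from the normal one. Without any calculation, 86–94% is 90 ± 4, not 90 ± 5.

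**Step 3: 200 patients, 100 of them abnormal.**
- Normal: 1.96 × √(0.09/100) = 5.88 points, so 84.1–95.9%. This reproduces the printed ±6% and 84–96%.
- Exact, 90/100: 82.38–95.10%.

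**Step 4: which denominator is meant.** If 200 and 400 were counts of abnormal patients, the normal half-widths would be 4.16 and 2.94 points. Both are narrower than the printed intervals (±6 and ±4), whereas half of each sample reproduces both. The figures therefore fit all patients at 50% prevalence, but the text does not say so.

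| Abnormal patients | Printed | Normal | Exact |
|---|---|---|---|
| 750 | 2.4%; 87.6–92.4% | 87.9–92.1% | 87.6–92.1% |
| 200 (of 400) | about 5%; 86–94% | 85.8–94.2% | 85.0–93.8% |
| 100 (of 200) | ±6%; 84–96% | 84.1–95.9% | 82.4–95.1% |

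**The case against.** The strongest reply is that none of this touches the design. The headline lower limit, 87.6%, is the correct exact lower limit; only the upper limit is off, and the printed interval is too wide rather than too narrow. The 88–92% in section 3.4.1.1 agrees with the normal interval, the exact interval and the synopsis interval after rounding, so it is not a further contradiction. The tumour-type figures are introduced conditionally; they set no quota and do not justify the overall size. All of this stands, and it is why the point is minor. What remains is that one printed interval matches no method tried and one statement disagrees with itself.

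Two stronger readings are tempting, and the document supports neither.

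- A reader might infer that the 200-patient interval is wrong or too optimistic. It follows from the protocol's own prevalence and the normal formula. Its lower limit is about 1.6 points too high (84% against 82.4%) only if the binomial interval is exact, which the protocol does not say. If 200 meant abnormal patients, the printed interval would be too wide.
- A reader might also take 15% off the 200 patients for incomplete data and conclude that the lower limit falls by up to 3 points. Section 3.4.1.1 does not call these patients recruited rather than assessable. The size of that drop also depends on rounding: 200 × 0.85 × 0.50 = 85 abnormal patients, and 90% of 85 is 76.5. The exact lower limit is 80.85% for 76/85 and 82.3% for 77/85.

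**Conclusion.** The point holds as a minor reporting error.

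- **Headline interval:** 87.6–92.4% is not reproduced. The half-width is 2.15 points by the normal method, and the upper limit is about 92.1% by either method, so the print is about 0.3 points too high. The error is conservative and affects neither the 750 nor the 1500.
- **400 patients:** the stated accuracy and the stated interval differ by about one point.
- **200 patients:** the figure is reproducible by the normal formula. It needs restating only if the analysis will use exact limits.

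The check assumes an observed sensitivity of exactly 90% and, for the tumour types, that half of the 200 or 400 patients are abnormal. That the two methods were mixed is inferred from the numbers; the document does not state how they were obtained. An analysis plan that is not at hand may name the interval method, so its absence here is not itself the finding. The disagreement among the printed figures is.

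**What to change.** Name one confidence-interval method in the precision section, the one the analysis will use, and restate all three figures with it in both the synopsis and section 3.4.1.1.

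- If exact binomial: 87.6–92.1% for 750 abnormal patients, 85.0–93.8% for 400 patients, 82.4–95.1% for 200 patients. Give these as intervals, because a single ± value cannot describe unequal arms.
- If normal approximation: 87.9–92.1%, 85.8–94.2% and 84.1–95.9%.

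State that 200 and 400 are assessable patients of whom 50% are expected to be abnormal.

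The cost is wording only: no change to recruitment, endpoints or analysis. With exact limits, the printed tumour-type lower limits fall by about 1 point (400 patients) and 1.6 points (200 patients).

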**These assessments will be performed blindly from the G8 and VES-13 answers.**

We will assess, for various thresholds of the assessed tool, the performances of the new screening tool compared to the reference one, thanks to the following parameters:

**The sensitivity (Se)**, defined by the proportion of patients registered as “requiring an CGA” with the screening tool, among patients having at least one abnormal CGA element;

**The specificity (Sp)**, defined by the proportion of patients registered as “not requiring a CGA” with the screening tool, among patients “having no abnormal CGA element”;

**Youden’s index (J)**, synthesizing the sensitivity and the specificity: J = Se + Sp – 1.

**The positive predictive value (PPV)**, defined by the proportion of patients “having at least one abnormal CGA element”, among patients registered as “requiring an CGA” with the screening tool.

**The negative predictive value (NPV)**, defined by the proportion of patients registered as “having no abnormal CGA element”, among patients “not requiring an CGA” with the screening tool;

**The positive diagnostic likelihood ratios (DLR+)**, defined by the ratio of positive tests in patients with the disease (true positive) out of positive tests in disease-free patients (FN of false positive).

**The negative diagnostic likelihood ratio (DLR-)**, defined by the ratio of negative tests in patients with the disease (false negative) out of negative tests in disease-free patients (true positive).

The area under the ROC curve will help determining the overall efficacy of the assessed test and determining the threshold value to increase simultaneously sensitivity and specificity of the new screening tool, or to maximise sensitivity while keeping a satisfying specificity. We will try to maximise sensitivity in order to decrease the G8 false negative rates, which would not thus benefit from the best management later.

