**3.3.2 Secondary endpoints**

3.3.2.1 Validation of the French version of the VES-13 screening tool

We will use the same validation criteria than for the G8 tool (see previous section): sensitivity, specificity, Youden’s index, predictive values, diagnostic likelihood ratios.

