**3.4.3 Statistical analysis**

The population of the study will be described broadly according to its clinical and sociodemographic characteristics in terms of size and ratio for the qualitative variables and in terms of distribution for the quantitative ones.

Missing data will be reported (by item and by questionnaire) thanks to frequency and percentage. The reasons for these missing data for any test will be described.

The following parameters will be estimated:

- **The sensitivity** will be estimated with the proportion of patients registered as “requiring a geriatric intervention” by the new tool, among the patients having at least one abnormal CGA element. A 95% CI will be reported (binomial distribution).
- **The specificity** will be estimated with the proportion of patients registered as “not requiring a geriatric intervention” by the new tool, among the patients having no abnormal CGA element.

A 95% CI will be reported (binomial distribution).

- **The positive predictive value** will be estimated with the proportion of patients having at least one abnormal CGA element, among the patients registered as “requiring a geriatric intervention” by the new tool. A 95% CI will be reported.
- **The negative predictive value** will be estimated with the proportion of patients having no abnormal CGA element, among the patients registered as “not requiring a geriatric intervention” by the new tool. A 95% CI will be reported (binomial distribution).
- **The ROC curve** representing graphically the sensitivity according to the (1 -specificity) for various thresholds of the assessed test will be represented graphically and help determine the area under the curve (AUC).
- **The internal consistency** will be assessed according to Cronbach’s alpha coefficient (Armitage & Berry, 2002).A 95% CI will be reported.
- **The reproducibility** will be assessed by the intraclass correlation coefficient for quantitative variables, with a 95% CI.
- **Scores between acknowledged subgroups** will be compared thanks to a variance analysis.
- **The area under the ROC curve** for G8 and VES-13 will be compared (Hanley et al, 1983).
- **We will assess whether using both screening tools together** (G8 and VES-13) helps obtaining a more effective screening tool compared to the sole use of one questionnaire (Macaskill et al., 2002).

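### The G8 versus VES-13 comparison is specified only through the AUC, although the protocol's priority is sensitivity; a paired comparison at the chosen cut-offs should be added

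*Protocol*

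**What the plan says.** Comparing the two tools is a secondary objective in the synopsis, with no measure or cut-off named. The measure comes under the statistical analyses: "Both G8 and VES-13 questionnaires will be compared thanks to their respective area under the curve". Section 3.4.3 agrees, saying that the area under the ROC curve "for G8 and VES-13 will be compared". The next item in both places asks whether the tools used together do better than one alone, which is a different question.

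The priority is stated three times. The synopsis has "The objective is to maximise the sensitivity of the new screening tool", section 3.4.1.1 has "The objective then is to maximise the sensitivity of the new screening tool", and section 3.3.1 gives the reason: "We will try to maximise sensitivity in order to decrease the G8 false negative rates". Section 3.3.1 gives the AUC two roles: to measure overall efficacy, and to help set a threshold. The threshold either raises sensitivity and specificity jointly "or to maximise sensitivity while keeping a satisfying specificity". No cut-off and no minimum specificity is given as a number, and section 3.4.3 refers to thresholds that the analysis will determine.

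For VES-13, section 3.3.2.1 says "We will use the same validation criteria than for the G8 tool". Both tools therefore get sensitivity, specificity, predictive values and likelihood ratios, each tool on its own. Binomial 95% CIs are planned for sensitivity and specificity.

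**The concern.** The AUC averages performance over all thresholds, including those nobody would use for screening. Two tools can share an AUC and still differ in the share of CGA-abnormal patients they miss at their working cut-offs. If so, the one planned test between the tools would tend to show no difference on a point that the protocol itself treats as most important.

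The separate estimates help only in part. Two intervals side by side give neither a difference nor an interval for it. The step 1 schedule in the synopsis has both tools completed at the same visit, and both are judged against the same reference. The data for a paired estimate will therefore exist, but the plan does not ask for one.

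**Working it through.** **1. The plan's own figure.** The inputs are 750 CGA-abnormal patients and an expected G8 sensitivity of 90% (synopsis and 3.4.1.1), so 675/750.
- The exact (Clopper-Pearson) 95% CI is 87.6% to 92.1%. The lower half-width is 90.0 − 87.63 = 2.37 points, which reproduces the stated 2.4% and lower limit of 87.6%. The synopsis's upper limit of 92.4% is that half-width mirrored.
- The rounded 88% to 92% in 3.4.1.1 also reproduces.
- 750/0.50 = 1500 assessable patients.

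This is the only sizing of the main analysis. No figure is given for G8 versus VES-13.

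**2. Can equal AUCs hide a gap in sensitivity?** Assume binormal curves: Se = Φ(a + b·Φ⁻¹(1 − Sp)), with a = Φ⁻¹(AUC)·√(1 + b²). The AUC of 0.80 and the slopes b are assumptions.
- b = 0.6: a = 0.8416 × √1.36 = 0.981
- b = 1.6: a = 0.8416 × √3.56 = 1.588

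| Specificity | Se, b = 0.6 | Se, b = 1.6 | Gap in 750 patients |
| --- | --- | --- | --- |
| 50% | 83.7% | 94.4% | 0.107 × 750 ≈ 80 |
| 60% | 79.7% | 88.2% | 0.085 × 750 ≈ 64 |
| 80% | 68.3% | 59.5% | order reversed |

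The AUC is the same throughout, yet the better tool depends on the cut-off.

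**3. What a paired comparison would give.** Assume 90% versus 86% (d = 0.04), n = 750 and two-sided 5%. The protocol states 5% without sidedness. Only the 90% and the 750 are the protocol's; the 86% and the discordance p_d are assumptions. McNemar power = Φ[(d√n − 1.96√p_d)/√(p_d − d²)], with d√n = 1.095.
- p_d = 0.12: (1.095 − 0.679)/0.344 = 1.21, power 89%
- p_d = 0.16: (1.095 − 0.784)/0.398 = 0.78, power 78%
- p_d = 0.20: (1.095 − 0.877)/0.445 = 0.49, power 69%

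Unpaired: the pooled SE is √(2 × 0.88 × 0.12/750) = 0.0168 and the unpooled SE is √((0.09 + 0.1204)/750) = 0.0167. Power = Φ[(0.04 − 1.96 × 0.0168)/0.0167] ≈ 66%.

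If the tools were independent given an abnormal CGA, p_d would be 0.9 × 0.14 + 0.1 × 0.86 = 0.212, with paired power 66%. Pairing then gains nothing; it gains when the tools agree more than that.

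**4. Precision of the difference.** The half-width is 1.96·√((p_d − d²)/n).
- p_d = 0.12: 1.96 × √(0.1184/750) = 2.5 points
- p_d = 0.20: 1.96 × √(0.1984/750) = 3.2 points

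**5. Smallest difference detectable with 80% power, G8 at 90%.** It is 4.8 points under conditional independence. It is 3.6 points if the smaller discordant cell is half of that expected under independence, and 2.7 points if a quarter. The planned sample can support the comparison.

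**The case against.** The best defence is that the sensitivity aim is worded for G8 and guides the choice of its threshold, not the contest with VES-13. Section 3.4.1.1 says that the two error rates are judged jointly, and 3.3.1 names the AUC as the measure of overall efficacy. With cut-offs taken from the study data, a difference in sensitivity partly reflects where each cut-off was placed, so a threshold-free measure is a defensible choice. Each tool's sensitivity is also visible with its interval, and the comparison is secondary.

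Much of this stands, and it rules out several stronger readings:
- **That the plan makes no use of the pairing.** The analysis of both tools together needs both results in the same patient. Whether the cited method for comparing AUCs allows for pairing cannot be judged from the document.
- **That overlapping intervals would hide a real difference.** The exact intervals for 675/750 and 645/750 (87.6 to 92.1 and 83.3 to 88.4) overlap, but overlap is not a test. An unpaired test gives z = 0.04/0.0168 = 2.38, p = 0.017.
- **That the AUC comparison is wrong or should be demoted.** It answers the objective on a legitimate global measure. Which measure comes first is a trade-off.
- **That a test at prespecified cut-offs is ready to run.** None is prespecified.
- **That 750 pairs are assured.** Section 3.4.1.1 defines an assessable patient by complete CGA and G8 data, without VES-13.

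What the defence does not remove is that the reason given for favouring sensitivity, missed patients, applies equally to choosing between tools. VES-13 is judged on the same criteria, and no estimate of the difference is planned. Nor is this only a detail left to an analysis plan, since the protocol fixes the comparison measure in two places.

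**Conclusion.** The point holds as a gap in a secondary analysis. The only specified comparison of G8 with VES-13 can show no difference while the tools differ in missed patients, by about 64 to 80 of 750 in the illustrations at 60% and 50% specificity. Those sizes rest on assumed curve shapes; the principle that equal AUC does not mean equal sensitivity does not.

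The gain in power from pairing is modest to clear (69% to 89% against about 66%) and depends on a discordance that the protocol does not give. The firmer gain is a direct estimate of the difference with its interval. The primary G8 estimate and its sample size are unaffected. This is a cheap improvement, not a flaw in the main result.

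**What to change.** In section 3.4.3, and in the matching line of the synopsis, keep the AUC comparison and add the following:
- Among patients with complete G8, VES-13 and CGA data, estimate the paired difference in sensitivity (CGA-abnormal) together with the paired difference in specificity (CGA-normal), each with a 95% CI and a McNemar test. Specificity must accompany sensitivity, because moving a cut-off can raise sensitivity alone.
- Use one cut-off per tool, either fixed in advance or chosen for both tools by the same stated rule before the comparison.
- If the cut-offs come from the same data, report this as a limit, for example by bootstrapping the cut-off selection with the comparison.
- Report how many patients enter the paired analysis.

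The cost is one two-by-two table per reference group and no new data or patients. The downside is two extra secondary tests and some optimism where cut-offs are data-derived.
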